### Data analysis

Participant flow will be reported in accordance with the CONSORT statement (Fig. 1). Baseline data will be described using summary statistics (means and standard deviations or numbers and percentages). The feasibility findings will be tabulated and associated graphical summaries of the key indicators of success will be presented. All anonymised participant data will be included in the efficacy analysis using an intention-to-treat approach.

Data from clinical outcome measures will be analysed using a linear regression model, allowing for baseline measurements of outcome, treatment assignment and NHS trust as covariates, at each assessment point separately. We will report 95% CIs and point estimates for effects instead of *p* values. The results will be used to provide an indication of the population effect size required for a future full-scale definitive trial. However, as a feasibility RCT, this study is not powered to find an effect.

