Given these encouraging findings, we aim to test the feasibility and acceptability of conducting a randomised controlled trial (RCT) to evaluate the Baby Triple P programme plus treatment as usual (TAU) in mothers with severe mental health difficulties admitted to one of two UK National Health Service (NHS) MBUs. Qualitative data from MBU staff and participants will be used to (1) assess the acceptability of the intervention and RCT procedures and (2) allow the refinement of the approach and intervention in preparation for a larger clinical trial. The overall aim of this feasibility study is to evaluate the Baby Triple P intervention in mothers with severe mental health difficulties in a MBU setting. The objectives of this feasibility RCT are:To examine the feasibility of the design and procedures of a future RCT.To examine the acceptability (to mothers and MBU staff) of the design and procedures of a future RCT.To examine the key cost indicators associated with the intervention.To involve service users to guide and inform the research.To examine the feasibility of (1) the recruitment methods (through the MBU ward staff and consultant psychiatrist), (2) recruiting sufficient numbers of mothers to be able to estimate an effect size for a future RCT, (3) the randomisation procedures in inpatient ward settings, (4) engagement and retention of mothers in the study (including completion of outcome measures) and (5) piloting data collection procedures (including frequency, duration and format of assessments).To examine mothers’ and MBU staff acceptability of Baby Triple P.To determine the best strategies to avoid or minimise possible contamination (e.g. mothers sharing the Baby Triple P workbook with mothers in the TAU group) or log such incidences.To assess the fidelity of Baby Triple P delivery on the MBU.To determine factors associated with engagement of mothers in and adherence to Baby Triple P.To examine attrition rates and causes and explore solutions to attrition.To determine the suitability of the primary and secondary outcomes and their respective measures for a future RCT alongside appropriate follow-up assessment time points.To explore the key cost elements and the appropriateness of the five level EQ-5D (EQ-ED-5 L) as a measure for a calculation of utility of the intervention in this population.

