**Fig. 2 Fig2:**
[figure not shown]
Schedule of enrolment, interventions and assessments

Assuming a drop-out rate of 10% between recruitment and randomisation in an inpatient setting, a maximum of 66 participants will be recruited and a maximum of 60 will be randomised after completion of baseline measures during their inpatient admission to a MBU. Participants will be randomly allocated, using an independent Clinical Trials Unit (CTU), to TAU or to TAU plus eight sessions of Baby Triple P. Additional sessions can be offered, for example, to conduct an initial assessment and, if required, the intervention can be delivered more flexibly.

Participants are followed up at 10 weeks post-baseline and at 6 months post-baseline. The end of treatment is not fixed but dependent on progress and participants’ capacity to engage, whereas assessment time points are fixed.

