### Randomisation

After written consent has been obtained, participants and MBU staff are asked to complete the first battery of outcome measures (i.e. the baseline assessment) before participants are randomly allocated to either TAU or TAU plus Baby Triple P. Randomisation is provided by an independent CTU with an allocation ratio of 1:1 and randomised permuted blocks of size 4 and 6, and is stratified by MBU site. Once the Manchester CTU informs the project manager of the arm to which the participant has been allocated, participants are informed of the randomisation outcome and provided with a randomisation leaflet outlining what they can now expect.

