It will be vital to identify the most appropriate, effective and sensitive outcome measures in order to detect meaningful participant reported and observer rated changes in parent and infant wellbeing resulting from the intervention. The use of observer rated measures is indicated given that participants are admitted to an inpatient unit due to a crisis that may affect their ability to concentrate on and complete self-report measures, but training is required to achieve inter-rater reliability across different raters. This study will enable us to establish which assessments are meaningful, relevant and appropriate during inpatient admission and after discharge.

The inclusion of service user consultants in various aspects of this study has been emphasised. As part of this, we will also assess the type of training and amount of support required for service user participation in the analysis of interview data and other study aspects. Staff views on the use of the intervention and the impact of the study on the MBU in combination with participant experiences will inform the development of a future RCT.

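### Between-arm estimates from at most 60 women are too imprecise to indicate the effect size for the definitive trial; the stated use should be reworded

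*Protocol article*

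**What the plan says.** The Data analysis section plans a linear regression for each clinical outcome, "allowing for baseline measurements of outcome, treatment assignment and NHS trust as covariates, at each assessment point separately". It then states: "We will report 95% CIs and point estimates for effects instead of" p values. The next sentence gives the estimates a purpose: "The results will be used to provide an indication of the population effect size required for a future full-scale definitive trial". The paragraph closes by acknowledging that a feasibility trial of this kind lacks the power to detect an effect.

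The same purpose appears among the objectives at the end of the Background, where one feasibility question concerns "recruiting sufficient numbers of mothers to be able to estimate an effect size for a future RCT".

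The size is fixed under Trial design, where the cap on randomisation reads "a maximum of 60 will be randomised after completion of baseline measures"; the recruitment figure behind that cap is stated as follows: "Assuming a drop-out rate of 10% between recruitment and randomisation in an inpatient setting, a maximum of 66 participants will be recruited". The Randomisation section gives an "allocation ratio of 1:1 and randomised permuted blocks of size 4 and 6". The article does not justify 60 by the precision of an effect estimate, names no minimum important difference, and does not say how the width of the interval would enter the sizing of the next trial.

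**The concern.** A sample size varies with the inverse square of the effect it is planned on, so error in the effect is magnified in the number of participants. About 30 women per arm give a wide interval for any between-arm difference. If that estimate guides the definitive trial, the trial may be planned with too little power to detect a worthwhile benefit, or made so large that it looks infeasible in a setting with few units. This is a use of the data that the article itself states, so it is not a detail left to an unseen analysis plan.

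**Working it through.** **Inputs from the article.** Maximum recruited 66, maximum randomised 60, allocation 1:1 (30 per arm), baseline-adjusted regression at each time point, 95% intervals.

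**Inputs assumed.** The article gives no follow-up loss, baseline-outcome correlation r or true effect. I take 24 to 30 analysed per arm (20% to 0% loss), r from 0 to 0.7, and a true standardised difference of 0.3.

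**The plan's own figure.** 60 × 1.10 = 66, and forward 66 × 0.90 = 59.4; 60 / 0.90 = 66.7, or 67. The 66 and 60 are acceptable and are no part of this point. There is no power or precision calculation to reproduce.

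**Precision.** SE = √(2/n) × √(1 − r²), and the half-width is 1.96 × SE. For n = 30 and r = 0: √(2/30) = 0.258, and 1.96 × 0.258 = 0.51.

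**Chance of a misleading estimate when the truth is 0.3.** P(estimate < 0.1) = Φ(−0.2/SE) and P(estimate > 0.6) = Φ(−0.3/SE).

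| Analysed per arm | r | SE | 95% half-width (SD) | P(estimate < 0.1) | P(estimate > 0.6) |
|---|---|---|---|---|---|
| 30 | 0 | 0.258 | 0.51 | 22% | 12% |
| 30 | 0.5 | 0.224 | 0.44 | 19% | 9% |
| 30 | 0.7 | 0.184 | 0.36 | 14% | 5% |
| 24 | 0 | 0.289 | 0.57 | 24% | 15% |
| 24 | 0.5 | 0.250 | 0.49 | 21% | 12% |
| 24 | 0.7 | 0.206 | 0.40 | 17% | 7% |

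Using t rather than normal quantiles widens the extremes slightly, to 0.37 and 0.58.

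**Translation to the next trial.** At two-sided 5% and 90% power, with no allowance for attrition or covariates, n per arm = 2 × (1.960 + 1.282)² / d², about 21.0 / d².
- d = 0.3: 234 per arm.
- d = 0.1: 2,102 per arm, about nine times as many.
- d = 0.6: 59 per arm, about a quarter as many.

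The ratios are (0.3/0.1)² = 9 and (0.3/0.6)² = 0.25, so they do not depend on the power chosen.

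**Example.** An observed 0.4 with 30 per arm and r = 0.5 has a 95% interval of 0.4 ± 0.44, that is −0.04 to 0.84. The point estimate implies 132 per arm and the upper limit 30. At the lower limit there is no benefit to size for.

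**Simulation.** The definitive trial was sized at 90% power directly on the observed effect, with 24 or 30 per arm, r of 0 or 0.5, and assumed true effects of 0.3 to 0.5. The estimate was zero or negative in about 1% to 15% of runs. Among runs with a positive estimate, true power was below 80% in about 37% to 51%. The sample size was more than twice what was needed in about 25% to 28% and less than half in about 18% to 39%.

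**The case against.** The strongest defence is that the article promises little. It speaks of an indication, reports intervals in place of p values, and disclaims power in the next sentence. It nowhere says that the point estimate will be the sole input or that the interval will be ignored. The simulated error rates apply only if the next trial is powered on the raw estimate, a rule the article does not state. This stands as a limit on how strongly the point can be put: mis-sizing is a real risk, not a certainty. It does not dispose of the point. Those cautions govern inference within this trial, while the estimate is still directed to the next one with no rule for carrying its uncertainty forward.

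Two stronger readings are tempting and are not supported.

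- A reader might infer that the paragraph contradicts itself by disclaiming power and still using the estimate. It does not: power concerns testing, and an estimate with its interval can properly be reported from an unpowered study.
- A reader might infer from the Discussion's wish to "identify the most appropriate, effective and sensitive outcome measures" that the future primary outcome will be whichever measure shows the largest between-arm difference. The article states no such criterion. It also records completion and completeness of measures, and the staff-rated scales are collected only where feasible, so the number of competing comparisons is uncertain.

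It is also fair to say that the consequences fall on a later protocol, and that nothing in this trial's conduct or feasibility conclusions is affected. That limits the weight of the point but does not justify leaving the sentence as it is.

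**Conclusion.** The point holds as a fault in the stated use of the results, not in the analysis. Even at the favourable end of the assumed range, the half-width of 0.36 SD exceeds the illustrative true effect of 0.3 SD. Under that assumption, roughly one trial in seven to one in four would suggest at least nine times the sample needed. About one in twenty to one in seven would suggest about a quarter of it or less. These figures rest on the assumed loss, correlation and true effect and on normal approximations. The conclusion does not turn on any single value in the ranges shown. The wording should be changed before the estimates are used for planning.

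**What to change.** In Data analysis, replace the sentence on the population effect size with text to this effect:
- The target difference for the definitive trial will be a minimum important difference agreed with clinicians and service users.
- This trial will supply the SD (with allowance for its uncertainty), the baseline-follow-up correlation, data completeness and retention.
- The confidence interval for the effect will be used only to check whether the target difference is excluded.

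Amend the objective on estimating an effect size to match. How the allowance for uncertainty in the SD is made is a matter of convention and can be left to the investigators.

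The article gives no target difference, so no single sample size follows. For illustration only, at 90% power and two-sided 5%, targets of 0.3, 0.4 and 0.5 SD need 234, 132 and 85 per arm.

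The cost is wording: the data, models and reported intervals are unchanged. The downside is that a target difference must be agreed separately; the service user group already in place could contribute to that.

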### Economic evaluation

To determine the feasibility of conducting a full economic evaluation, data required to identify key drivers of costs associated with the Triple P intervention and TAU will be collected. This will include the resources required to deliver the intervention and NHS and social care services (inpatient, outpatient, primary and community care services) used by participants in both treatment groups during the study follow-up period. The EQ-5D-5 L [62] will be used to estimate quality-adjusted life years based on health status and associated utility tariffs, as per the approach recommended by NICE at the time of the analysis [6]. The quality and completeness of resource use and health status data will be reported. Utility values will be compared with scores on the MEQ [55] to determine whether the characteristics (e.g. direction) of any observed health outcomes are comparable according to both measures.

### Qualitative data analysis

All interviews will be digitally recorded, transcribed verbatim and subject to framework analysis to allow both inductive and deductive coding [69]. An initial coding framework will be developed to reflect key service and service user-determined topics covered by the interview schedule. Following data familiarisation, this framework will be augmented and extended to encompass new emerging themes. Coding will be undertaken by the first author and/or a member of the research team, experienced and trained in qualitative data analysis, and in consultation with our service user consultants to capture potentially different perspectives.

Initially, a subset of transcripts will be coded independently and findings will be discussed to develop a shared theoretical framework between academic and service user researchers. This framework will then be applied to the remaining transcripts. As the constant comparison of new data occurs, the framework will be amended and refined to enable the introduction of new codes or the deletion of redundant codes. Data will be interpreted and analysed within the final framework to structure and compare participant and staff views about the intervention.

Analysis will be overseen by research team members with qualitative data analysis experience. Regular meetings will ensure that the emerging codes are grounded in the original data. The trustworthiness of the final analysis will be enhanced through the integration of data from different stakeholders and through researcher triangulation.

## Discussion

This will be the first study to examine the feasibility and acceptability of conducting a RCT of a manualised parenting and psychological intervention for women admitted to one of two inpatient MBUs. It is also the first feasibility RCT to examine the possible benefits of a manualised parenting intervention in an acute inpatient setting with this population [18, 70]. The intervention is first offered in the MBU and, depending on admission time, it continues following discharge, offering continuity of care to participants whose care has to be transferred from inpatient acute psychiatric care to community care following MBU discharge. It is anticipated that routine post-discharge care will vary depending on local psychiatric and psychological arrangements and support.

This study allows for the exploration of pragmatic issues that will inform a larger RCT. This feasibility study will allow us to assess the suitability of the Baby Triple P programme for this clinical population and, if necessary, identify how it can be refined and tailored to meet participant capabilities and needs during an inpatient admission in terms of both its content and the practicalities of its delivery (e.g. by refining the length and number of sessions per week and/or mode of delivery). As participants will present with a range of perinatal mental health diagnoses and difficulties as well as parenting concerns and levels of confidence, the appropriateness of the content and practicalities of attending sessions will be examined in interviews.

The information gained from this study will provide an indication of what recruitment methods work or do not work in this setting and with this clinical population, enabling us to identify any participant-, staff- or service-related barriers to recruitment alongside solutions to overcoming these. It will help us to determine whether it is possible to recruit a large enough sample for a full-scale RCT and in what timescale. In addition, the adequacy of the recruitment sites can be examined in order to determine the characteristics of the sites that make them most suitable for a future RCT of this intervention. The inclusion and exclusion criteria will be scrutinised to determine whether it affords a large enough and suitable sample and whether revisions are needed for a future RCT (e.g. to eligibility criteria, etc.). An exploration of participant and staff facilitators for and barriers to study engagement is likely to highlight practicalities that need to be considered when embedding a RCT in this setting.

Inpatient psychiatric wards can be challenging environments for patients to recover in and for staff to work in. Ward acuity and severity and expression of mental health problems alongside staffing issues can influence the availability of routine psychosocial and psychological support for women admitted to a MBU, whilst the baby’s needs also determine if the mother can access any support being offered. Hence, it is anticipated that TAU across both MBUs and outpatient routine care will vary. As evidence of cost-effectiveness is essential to inform future NHS policy, this study will determine the best approach to obtain the data needed to conduct a robust economic evaluation of the intervention in a full RCT. Furthermore, this study will allow us to collect data on what aspects of ward activities have to be considered in order to identify the best approaches (e.g. the recruitment procedures, the completion of measures, the intervention delivery and/or format) to implement this intervention successfully.

It will be vital to identify the most appropriate, effective and sensitive outcome measures in order to detect meaningful participant reported and observer rated changes in parent and infant wellbeing resulting from the intervention. The use of observer rated measures is indicated given that participants are admitted to an inpatient unit due to a crisis that may affect their ability to concentrate on and complete self-report measures, but training is required to achieve inter-rater reliability across different raters. This study will enable us to establish which assessments are meaningful, relevant and appropriate during inpatient admission and after discharge.

The inclusion of service user consultants in various aspects of this study has been emphasised. As part of this, we will also assess the type of training and amount of support required for service user participation in the analysis of interview data and other study aspects. Staff views on the use of the intervention and the impact of the study on the MBU in combination with participant experiences will inform the development of a future RCT.

### Dissemination policy

The research team intend to disseminate outcomes from this study in peer-reviewed open access journals and at relevant conferences. Participants will be provided with a lay summary of the findings if they indicated that they wish to receive this information.

### Trial status

Recruitment started in November 2016 and is ongoing.

## Abbreviations

CGI: The Clinical Global Improvement Scale
CTU: Clinical Trials Unit
DASS: Brief Depression, Anxiety and Stress Scale
EQ-5D-5L: Five level EQ-5D
MBU: Mother and Baby Unit
MEQ: Maternal Efficacy Questionnaire
NHS: National Health Service
NICE: The National Institute for Health and Care Excellence
PBQ: Postpartum Bonding Questionnaire
RCT: randomised controlled trial
SMI: severe mental illness
TAU: treatment as usual
